### Stopping rules for participants and trial

#### Stopping trial intervention

If the participant meets any of the following conditions, the treating physician will stop the trial intervention and record the date and the reason. However, the participant is not considered to have dropped out of the study at this stage and will receive the protocol assessments:
The participant wishes to withdraw from the trial intervention and/or treatment with lithium carbonateThe treating physician judges that it is difficult to continue the trial intervention and/or lithium carbonate owing to the occurrence of serious adverse eventsThe treating physician judges that the trial intervention and/or lithium carbonate should be stopped for clinical reasons other than serious adverse eventsThe Steering Committee judges that the trial intervention or lithium carbonate should be stopped for any reason

#### Stopping assessment

If the participant withdraws their consent to the protocol assessments, the participant will be excluded from analyses regardless of whether he/she continues the trial intervention and/or lithium carbonate.

The participant will be excluded from analyses if, after informed consent, it is found that the participant did not meet the eligibility criteria. In this case, the participant will not be considered to have stopped the trial intervention or the protocol assessments.

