#### Primary outcome

The primary outcome is the achievement of therapeutic serum lithium concentration between 0.4 and 1.0 mEq/L at 18 months after informed consent. If a participant withdraws during the follow-up period or the result of the final blood test is not available, he/she will be regarded as not having achieved the primary outcome, because unavailability for the final serum lithium measurement strongly implicates that the patients is not adherent. However, the validity of this assumption will be tested in a sensitivity analysis using multiple imputation (see “Statistical analyses”).

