### Statistical analysis

All analyses will be conducted based on the intention-to-treat principle. The primary outcome will be analyzed from the full analysis set using logistic regression and reported with the odds ratio, *p* value, and 95% confidence interval. The model includes the primary diagnosis based on PRIME-MD (major depression, bipolar I disorder, or bipolar II disorder) and baseline serum lithium (0.4–1.0 mEq/L; < 0.4 mEq/L; or > 1.0 mEq/L). The validity of our assumption equating missing the final serum lithium measurement with not achieving the primary outcome will be examined in sensitivity analysis using multiple imputation. Secondary analyses and subgroup analyses will be conducted to supplement the primary analysis and explore a deeper understanding of the study questions. As secondary and subgroup analyses are exploratory, we will not adjust the significance level for multiple testing. All statistical tests will be two-sided and *p* values <0.05 will be considered statistically significant. The details of the statistical analysis will be decided within the statistical analysis plan, which will be reviewed and approved by the trial statistician and become publicly available before outcomes of the last participant are registered and therefore while the treatment allocation is still unknown. No interim analyses will be conducted in this trial.

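### Randomized participants who withdraw consent to assessments fall under two incompatible rules, and the post-consent exclusions are not confined to the time before randomization, contrary to intention-to-treat

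*Protocol article*

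**What the plan says.** Four statements in the protocol article bear on who is in the primary analysis.

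- *Primary outcome*: "If a participant withdraws during the follow-up period or the result of the final blood test is not available", then "he/she will be regarded as not having achieved the primary outcome". The stated reason is that an unavailable final lithium value points to non-adherence. A multiple-imputation sensitivity analysis is to test that assumption.
- *Stopping assessment*: "If the participant withdraws their consent to the protocol assessments, the participant will be excluded from analyses". This holds whether or not the person continues the reminders or lithium. The same section adds: "The participant will be excluded from analyses if, after informed consent, it is found that the participant did not meet the eligibility criteria".
- *Stopping trial intervention*: for someone who stops only the reminder or lithium, "the participant is not considered to have dropped out of the study at this stage and will receive the protocol assessments".
- *Statistical analysis*: "All analyses will be conducted based on the intention-to-treat principle", and "The primary outcome will be analyzed from the full analysis set using logistic regression". The article does not define the full analysis set.

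Two design facts matter. Under *Randomization*, allocation takes place at the first scheduled visit 4 to 8 months after consent, so the period after consent lies partly before and partly after randomization. Under *Masking*, the treating physician and the participant know the allocation.

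**The concern.** Once randomized, a participant who withdraws consent to the assessments has withdrawn during follow-up and will normally have no final lithium value. One section keeps that person in the denominator as a failure; another deletes the person. The analyst cannot do both, and the article states no precedence.

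Deletion is also the choice that conflicts with the intention-to-treat statement. In an open-label trial the decision to withdraw can depend on the arm. By the protocol's own reasoning about non-adherence, it can also be related to the outcome. Removing such people after randomization can shift the odds ratio in either direction. The ineligibility exclusion raises the same issue because its wording sets no end point at randomization.

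At stake is the composition of the primary analysis population, and hence the primary estimate, in a trial of 120 people.

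**Working it through.** **1. Which participants are affected.**

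| Situation | *Primary outcome* | *Stopping assessment* | Conflict |
|---|---|---|---|
| Stops only reminder or lithium | assessed as usual (see *Stopping trial intervention*) | not triggered | no |
| Stays in the study, final test missing | not achieved | not triggered | no |
| Withdraws consent to assessments before randomization | no allocation yet | excluded | no; harmless to intention-to-treat |
| Withdraws consent to assessments after randomization | not achieved | excluded | **yes** |
| Found ineligible before randomization | no allocation yet | excluded | no; harmless |
| Found ineligible after randomization | outcome counts | excluded | **yes, with intention-to-treat** |

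Stopping the intervention is expressly not dropping out. Withdrawal from assessments is therefore the most natural meaning of withdrawal in *Primary outcome*, and the fourth row is not a remote case.

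**2. Whether another provision resolves it.** The full analysis set is named but not defined in the article. Multiple imputation replaces missing final values for people in the analysis set; people deleted under *Stopping assessment* are not there to be imputed.

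**3. Size.** The article gives no expected number of consent withdrawals, so there is no planned figure for this to reproduce. It does give the dropout allowance: 54 / (1 − 0.10) = 60 per group, 120 in total. The step reproduces and supplies the 60 per arm used below. All withdrawal counts by arm are assumptions, and treating the whole 10% dropout as consent withdrawal is an upper case.

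*Illustration A: same success among completers.* Assume 65% success among completers in both arms, with 3 withdrawals in the intervention arm and 9 in control (12 of 120 = 10%).

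- Count as failure: 0.65 × 57/60 = 61.75%; 0.65 × 51/60 = 55.25%; difference +6.5 points.
- Exclude: 65% versus 65%; difference 0.
- Balanced, 6 versus 6: 0.65 × 54/60 = 58.5% in both arms under the failure rule and 65% in both under exclusion; difference 0 either way.
- Each one-participant imbalance is worth about 0.65/60 = 1.1 points.

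*Illustration B: the planning rates of 80% and 55% among those who stay.* Exclusion always gives 25 points (odds ratio (0.80/0.20)/(0.55/0.45) = 3.27). Under the failure rule:

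| Withdrawals, intervention vs control | Intervention | Control | Difference |
|---|---|---|---|
| 6 vs 6 | 0.80 × 54/60 = 72.0% | 0.55 × 54/60 = 49.5% | 22.5 points |
| 9 vs 3 | 0.80 × 51/60 = 68.0% | 0.55 × 57/60 = 52.25% | 15.75 points |
| 3 vs 9 | 0.80 × 57/60 = 76.0% | 0.55 × 51/60 = 46.75% | 29.25 points |

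With 6 versus 6 the odds ratio is (0.72/0.28)/(0.495/0.505) = 2.62. When the arms truly differ, the choice of rule therefore matters even with balanced withdrawal.

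*Illustration C: no true effect, withdrawers all non-achievers.* Take 33 achievers of 60 in each arm, with 9 versus 3 withdrawals. The failure rule gives 55.0% in both arms, difference 0. Exclusion gives 33/51 = 64.7% against 33/57 = 57.9%, a difference of 6.8 points and an odds ratio of (33/18)/(33/24) = 1.33. With 6 versus 6, exclusion gives 33/54 = 61.1% in both arms and no difference.

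**The case against.** The best defence is that the two sections form a general and a specific rule: *Stopping assessment* governs revoked consent, and *Primary outcome* governs every other withdrawal or missing test. The definition of the full analysis set is properly left to the statistical analysis plan. Much of the period after consent precedes randomization, where exclusion does no harm. The data manager, statistician and steering committee are masked. Scoring someone who only declines assessments as a failure is itself a choice, since the non-adherence rationale need not apply to that person.

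Part of this stands. The conflict is confined to randomized participants, the size is unknown, and the failure rule rests on an assumption, which is why those participants belong in the imputation analysis. The rest does not remove the point. The specific-over-general reading is stated nowhere, and if adopted it leaves a post-randomization exclusion beside an intention-to-treat statement. Masking the central staff does not affect a withdrawal that arises between a physician and a patient who both know the arm. An analysis plan can define the set only by overriding one of the two rules in the article.

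A reader might go further in three ways that the documents do not support:

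- *That everyone who withdraws is deleted.* People who stop only the reminder or lithium are kept and assessed, and a missed final test counts as failure.
- *That physicians enter ineligibility after seeing the allocation.* The not-eligible entry under *Eligibility check and registration* concerns candidates at registration. The concern about late ineligibility rests only on the open-ended wording of *Stopping assessment*.
- *That illustration A proves the exclusion rule biased, or predicts a 6.5-point error.* There completers do equally well and it is the failure rule that produces the gap; illustration C shows the reverse. Together they show sensitivity to the rule, under invented splits.

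**Conclusion.** The point holds for two groups: randomized participants who withdraw consent to assessments, and participants found ineligible after randomization. For the first, the article fixes two incompatible rules without precedence. For both, exclusion contradicts the intention-to-treat statement, and the planned multiple imputation cannot undo it. This conclusion rests on the text alone and needs no assumption about numbers.

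The effect on the estimate cannot be determined from the documents. With assumed 3 versus 9 withdrawals and equal success among completers, the rules differ by 6.5 points, about a quarter (6.5/25 = 26%) of the planned 25-point difference. With balanced withdrawals in that setting they do not differ. Few consent withdrawals would mean a small effect; many, or unbalanced ones, could matter for the primary result.

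**What to change.** Amend *Stopping assessment* and carry the same wording into the statistical analysis plan:

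1. Its exclusions apply only before randomization.
2. Every randomized participant is in the full analysis set, in the assigned arm.
3. Withdrawal from assessments or a missing final test counts as not achieved, as *Primary outcome* already says, and these participants are included in the multiple-imputation analysis.
4. Data recorded before withdrawal are kept.
5. Only a participant who revokes use of all their data is removed, with numbers reported by arm.
6. A participant found ineligible after randomization stays in the primary analysis.

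The cost is wording only. The downside is that a few ineligible participants are retained. The article reports recruitment still under way and an analysis plan to be made public while allocation is unknown, so on that timetable one rule can be set without knowledge of results.

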#### Stopping criteria for the trial

The Steering Committee will stop the trial upon advice or orders from the Ethics Committee if either of the following conditions are met:
Any serious problem in the quality, safety, and efficacy of the trial intervention and/or lithium carbonateWhen the Ethics Committee issues and order for changes to the protocol that are unacceptable to the researchers

The decision to stop the trial, and the reason for this, will be reported to the Ethics Committee and research staff as soon as possible.

### Data collection and management

All the patient data are stored in the EHR and the password-protected trial program on a local server automatically stores the information on screening, randomization, and the intervention. After trial completion, researchers manually extract anonymized patient data from the trial program and EHR, check the data quality, and finalize the data set.

### Statistical analysis

All analyses will be conducted based on the intention-to-treat principle. The primary outcome will be analyzed from the full analysis set using logistic regression and reported with the odds ratio, *p* value, and 95% confidence interval. The model includes the primary diagnosis based on PRIME-MD (major depression, bipolar I disorder, or bipolar II disorder) and baseline serum lithium (0.4–1.0 mEq/L; < 0.4 mEq/L; or > 1.0 mEq/L). The validity of our assumption equating missing the final serum lithium measurement with not achieving the primary outcome will be examined in sensitivity analysis using multiple imputation. Secondary analyses and subgroup analyses will be conducted to supplement the primary analysis and explore a deeper understanding of the study questions. As secondary and subgroup analyses are exploratory, we will not adjust the significance level for multiple testing. All statistical tests will be two-sided and *p* values <0.05 will be considered statistically significant. The details of the statistical analysis will be decided within the statistical analysis plan, which will be reviewed and approved by the trial statistician and become publicly available before outcomes of the last participant are registered and therefore while the treatment allocation is still unknown. No interim analyses will be conducted in this trial.

### Monitoring

#### Data monitoring

The data manager, in conjunction with the clinical management team, conducts weekly central monitoring and annual on-site monitoring in the trial. In the central monitoring, we monitor the number of patients screened, eligible, included, and allocated by the weekly central monitoring. In addition, the data manager conducts on-site monitoring every 6 months after registration of the first case, to check the logistics, such as the informed consent document.

### Site audit

No formal site auditing will be conducted, because the trial comprises only a minimally invasive intervention.

### Harms

Adverse events are defined as follows: any undesirable or unintended signs including anomalies in clinical laboratory evaluations, symptoms, or diseases among participants, regardless of whether there is a causal relationship with the treatment. The treating physician will provide and/or arrange appropriate treatments, including hospital admission if necessary. Because adverse events, including toxicities of lithium carbonate, are monitored as part of routine care, study-specific monitoring will not be required.

When a serious adverse event occurs, the treating physician must take all the necessary and appropriate measures to ensure the safety of the participant. The treating physician must also notify the principal investigator and report to the chief study investigator at Toyooka Hospital within 24 h. The principal investigator must notify the Ethics Committee of the Graduate School of Medicine, Kyoto University Graduate School of Medicine within 72 h. The chief study investigator at Toyooka Hospital must report to its own Institutional Review Board (IRB) and, if it concerns an unforeseeable serious adverse event, must report to the Ministry of Health, Labour and Welfare (MHLW). A serious adverse event is defined as one that may lead to death or to continuous severe impairment, depending on the patient’s conditions and circumstances.

### Foreseeable adverse events

No adverse events are foreseeable for the trial intervention itself, except for the potential burden and complications of blood tests. All drugs, including lithium carbonate, are within the approved dosages and indications according to the MHLW.

The foreseeable side effects of lithium carbonate, as described in the package insert, are as follows:

Major side effects: Tremor (4.6%), dry mouth (2.4%), and diarrhea (1.2%). Serious side effects: Lithium intoxication (unknown frequency); malignant syndrome (unknown frequency); sick sinus syndrome and bradycardia (unknown frequency); nephrotic diabetes insipidus (unknown frequency); acute kidney injury, interstitial nephritis, and nephrotic syndrome (unknown frequency); hypothyroidism and thyroiditis (unknown frequency); hyperparathyroidism (frequency unknown); and dementia and impaired consciousness (frequency unknown).

### Ethics and dissemination

#### Adherence to the study protocol

All researchers participating in the trial will place the safety and human rights of the participants at the highest priority and will adhere to the study protocol, as long as it does not compromise their safety and human rights.

#### Regulations to be adhered to

All researchers participating in the trial will abide by the Declaration of Helsinki and its amendments, and by the Ethical guidelines for medical and health research involving human subjects (2017 revision, Ministry of Education, Culture, Sports, Science and Technology, and MHLW).

### Approval by the Institutional Review Boards

The trial has been approved by the Ethics Committee of the Kyoto University Graduate School of Medicine (registration number: C1401) and the Institutional Review Boards of Toyooka Hospital (registration number: 180).

### Protocol amendments

Any changes to the study protocol will be reported to the Ethics Committee of the Kyoto University Graduate School of Medicine for approval. If approval is granted, approval for the study protocol change will subsequently be sought from the Institutional Review Board of Toyooka Hospital. Changes will then be disseminated to the research staff, and, where necessary to the study participants.

### Informed consent

#### Procedures for informed consent

The treating physician must make sure that the participant has understood the contents of the trial and must obtain written informed consent from the participant. The treating physician must seek repeat consent when the research protocol is revised, and any invasion or possible disadvantage is applied to the participant who has already consented.

### Confidentiality

All researchers and contractors of the trial must strictly manage participants’ personal information in adherence with the Ethics Guideline for Clinical Research and Act on the Protection of Personal Information. The data manager will delete site-specific patient IDs and add study-specific patient IDs at the time of data retrieval from Toyooka Hospital. Before the data manager retrieves the data, the data manager and the chief study investigator at Toyooka Hospital will ensure the data anonymity. The chief study investigator will keep the correspondence table up to date, including both the study-specific and the site-specific patient IDs at Toyooka Hospital. The data manager and the trial statistician will have access only to anonymized data and will not have access to the participants’ personal information. The media will be stored in a locked cabinet in the office of the Department of Pharmacoepidemiology, School of Public Health, Department of Pharmacoepidemiology, Graduate School of Medicine/School of Public Health, Kyoto University, for 10 years after the publication of the main results and will then be discarded.

### Access to the data

All members of the Steering Committee will have full access to all the final dataset.

### Ancillary and post-trial care

All participants will receive standard care during and after the trial.

#### Exemption of medical expenses and rewards

As all the diagnostic tests and treatments in the trial are within the MHLW-approved dosage and administration, medical expenses will be covered in the usual way through the participant’s health insurance and copayment. Participants will not receive any reward or exemption for any tests or treatments.

#### Compensation for adverse events

As all the diagnostic tests and treatments in the trial are conducted in accordance with the indications and dosage approved by the MHLW, the costs of care for any adverse events will be covered by the participant’s health insurance and copayment. We will not contract private health insurance for clinical research because the trial involves only a minimally invasive intervention.

### Dissemination policy

The protocol will be published in an English-language academic journal and presented at a scientific conference. The synopsis will be available from the website of the Department of Health Promotion and Human Behavior, Department of Pharmacoepidemiology, Graduate School of Medicine/School of Public Health, Kyoto University, and Toyooka Hospital. The trial results will be disseminated through academic journals and conference presentations. A summary of study results will be disseminated on the website listed above for dissemination to trial participants.

Authorship for the primary and secondary results will be determined by all members of the Steering Committee. If the chief study investigator, participating physicians, and other members of the Steering Committee do not appear as co-authors, they will be listed at the end of the article. Such authors may be listed as co-authors in some journals, but not in others.

After the publication of the main findings, we will register the anonymized dataset in UMIN-Individual Case Data Repository (ICDR) (http://www.umin.ac.jp/icdr/index-j.html). Only researchers who are certified by the Steering Committee will be allowed access the data.

## Discussion

KONOTORI is an EHR-nested, parallel-group, superiority RCT examining the effectiveness of the reminder system for serum lithium monitoring. This trial includes some prominent characteristics.

First, as mentioned previously, the trial program embedded with the EHR automatically prompts for screening, conducts random allocation, outputs reminders, and collects data without extra cost and time burden in everyday clinical practice. Embi et al. demonstrated a 10-fold increase in referral rate and the doubling of recruitment with an EHR-nested recruiting system [14]. Recently, several EHR-nested RCTs have been implemented for the assessment of the effectiveness of various interventions, such as alerts on kidney injury, warnings for harmful drug-drug interactions, laboratory test abnormalities, personalized antibiotics prescription feedback, or dosing errors [7, 9, 11]. The REDUCE trial is ongoing to reduce unnecessary antibiotic prescriptions for respiratory tract infections in general practice, with a monthly feedback, educational, decision support tool, and webinar using EHR [8]. Similarly, the Standard and new antiepileptic drugs II (SANAD II) trial is assessing the clinical and cost effectiveness of antiepileptic treatments for patients with newly diagnosed epilepsy [10]. However, the feasibility of EHR-nested RCTs in Japan is unclear, because the aforementioned trials were conducted in Western countries, mostly in the USA and UK. The KONOTORI trial will be the first EHR-nested RCT not conducted in a Western country.

Second, in our sample size calculation with an EHR-based administrative database including Toyooka hospital, about 45% of patients had serum lithium of < 0.4 mEq/L or > 1.0 mEq/L. We assumed that the infrequent monitoring may partially have caused such deviation. Then, we expect that more frequent monitoring triggered by the reminders may be useful to maintain serum lithium within the appropriate range and achieve subsequent clinical outcomes. The two-step reminders (A and B) are to remind not only the physicians but also the patient. The reminders may, through the increased frequency of the reminder to the physician, the increased awareness on the part of the physicians, the increased recommendation from the physician to the patients based on such reminders, and/or through increased adherence on the part of the patients resulting from such interactions with the physician, help achieve the primary outcome of the therapeutic serum concentration. Then, it is not feasible to mask the patient, because we remind not only the physician to increase the frequency but also the patient to improve adherence. If the automated reminder system is found to be effective for achieving the appropriate serum lithium level in patients taking lithium carbonate in this study, this may contribute directly to improvement in the quality of clinical practice, because its implementation does not require additional effort by clinicians. On the one hand, the trial was so designed to pragmatically examine the net effect of this procedure and not to explore the mechanisms by administering additional questionnaires to the physicians and the patients. This may be a weakness but also a strength in increasing the practicality of the trial and also the generalizability of the final findings through facilitated recruitment.

Finally, both the EHR-nested RCT scheme and the EHR-nested automated reminder system may be applicable in medical specialties other than psychiatry. Overall, if the EHR-nested trial is successful, it can be expected to contribute to the so-called learning healthcare system, where every clinical encounter in routine care can provide an opportunity to expand the evidence base for future health care [31] (Additional file 1).

